#### Confidence to provide Mental Health First Aid

One question will capture the business advisor’s confidence to help a person described in a vignette (see stigmatization) who has a mental health problem. The question will assess their confidence on a 5-point Likert scale (1 not at all confident, 5 extremely confident) and will be included in all three surveys.

#### Provision of Mental Health First Aid

Provision of mental health first aid questions will ask whether the business advisor has talked to a SME owner about their mental health over the past month using a 4-point Likert scale (1 never, 4 many times) [29]. A score of 1 will be given if they answer A Few or Many Times, with higher scores indicating they delivered mental health first aid more often. If they have talked with a SME owner client, they will be asked to indicate how many out of 12 actions they had taken. A score of 1 will be allocated to any action they have answered A Few or Many Times and summing these scores. Business advisors will complete these questions at baseline, 2- and 6-months follow-up.

### Secondary outcomes for SME owners

#### Trust

The degree of trust the SME owner has in their business advisor will be measured using the trust in Business Advisor Questionnaire [30]. This tool assesses three elements of trust: confidence, acting proactively and not exploiting vulnerabilities. In addition, the SME owner’s confidence in the services (i.e., beyond compliance services) offered by the business advisor will be assessed. Eleven questions will be used to assess these elements on a 5-point Likert scale (1 strongly disagree, 5 strongly agree) with a higher total score indicating a more trusting relationship. Factor loadings for these items range from 0.43 to 0.95 and show good reliability, with Cronbach’s alpha of 0.931 to 0.937. The items have demonstrated content validity, i.e., they assess all relevant components of trust [30]. The SME owner will answer these questions at baseline, 6- and 12-months follow-up.

#### Quality of the relationship

At each of the data collection points, the quality of the relationship between the SME owner and their business advisor will be measured using a Quality of the Relationship Questionnaire. The questions will measure the SME owner’s satisfaction on how aware their business advisor is about their wellbeing, whether they can turn to their advisor when things are going badly, and whether they seek their advice on a range of business matters. Six items will be used from a newly developed tool by the principal investigators (AN, GT) with factor loadings of 0.81 to 0.87, and uniqueness scores of 24 to 34%, indicating they are highly relevant to measuring the quality of relationship. All items are on a 7-point Likert scale (1 strongly disagree, 7 strongly agree) with a higher total score indicating a higher quality relationship.

#### Financial wellbeing

The financial wellbeing of the SME owners will be measured at each time point using the Perceived Financial Wellbeing Questionnaire [31]. The SME owners must consider how much they agree with 5 statements such as “I am behind with my finances”. Their answers will be scored on a 5-point Likert scale (1 strongly agree, 5 strongly disagree) and a lower total mean score will indicate a more positive outlook. Perceived financial well-being is a strong predictor of overall well-being and the items have a Cronbach’s alpha of 0.86 to 0.94 [31]. The questionnaire has demonstrated discriminate and incremental validity [31].

#### Financial distress

The financial distress of the SME owners will be measured using the Financial Distress/Financial Wellbeing Scale [32]. This comprises of 8 items designed to assess how positively they view their financial situation, on a score from 1 to 10. A higher mean total score indicates no financial distress/high financial well-being. It has robust internal reliability, with a Cronbach’s alpha of 0.956 indicating that the items consistently yield similar scores. Factor loadings of the 8-items range from 0.83 to 0.93, indicating the measurement of only one dimension and have shown robust content validity [32]. The SME owner’s financial distress will be assessed at baseline, 6- and 12-months follow-up.

#### Psychological distress

Psychological Distress of the SME owners at all time points will be measured using the Kessler 6 (K6) [33]. This broad screening scale assesses individuals for psychological distress as defined as a K6 score ≥ 13. The K6 asks respondents, “In the past four weeks how often did you feel the following: nervous, hopeless, restless, fidgety, worthless, depressed and felt that everything was an effort?” For each question, a value of zero to four is assigned (0 none of the time, 4 all the time), and the total score is summed out of 24 with a higher score indicating greater psychological distress. The scale has demonstrated excellent internal consistent reliability (Cronbach’s alpha = 0.89) and convergent, incremental and divergent validity [33]. 

#### Quality of life

Quality of Life questions will measure the general health of the SME owners at all time points. The Short Form-12 questionnaire (SF-12) produces two summary scores – a mental component score (MCS-12) and a physical component score (PCS-12). This test has a test re-test reliability of 0.76 to 0.89 for the mental (MCS-12) and physical (PCS-12) health components [34]. Both components can discriminate among groups known to differ in their physical and mental conditions, yielding relative validities of 0.63 to 1.07 [34]. The answers are weighted and the results are presented relative to the United States population profile at the time of the original publication in 1994. A higher score for MCS and PCS indicates a better health state.

#### Help Seeking Behaviour

Actual Help Seeking Behaviour questions will assess the SME owners behaviour of actively seeking assistance for any mental health problems at all time points [35]. The scale covers informal and formal assistance, as well as physical and emotional aspects of help-seeking behaviour. The participant is asked to select from a list of people they have gone to for advice or help in the past two-weeks.

Other outcomes will be included in the surveys to test longitudinal models designed by the investigators (AN and GT) that describe how the characteristics of an individual business advisor or SME owner (e.g., resilience) and working conditions (e.g., autonomy, workload) may impact their financial and/or mental wellbeing. These outcomes are described in Supplementary file 3.

### Process evaluation

The second aim of this project is to undertake a comprehensive, research-to-practice process evaluation to ensure that the assessment of Counting on U extends beyond the effectiveness of the interventions [36, 37]. We will draw on the research translation evaluation framework, RE-AIM (i.e., Reach, Effectiveness, Adoption, Implementation, and Maintenance), to explore: the processes used to Reach a nationally representative sample of practising business advisors; how Effective and relevant the intervention is to business advisors and SME owners, and what factors helped or hindered the business advisors to apply what they learnt; what factors influenced the professional member bodies to Adopt the training; whether the instructors Implemented the training in the way it was intended, and; why or why not the professional member bodies decide to Maintain the training as part of their ongoing career professional development program and whether any benefits of the training are Maintained long-term.

To measure these outcomes, field notes and qualitative structured interviews via zoom will be conducted during the training with the business advisors, SME owners, instructors, training vendors, and professional member organization representatives who will assist with the recruitment of business advisors. A risk mitigation-strategy will be designed for the researchers to use in case any interviewee is experiencing poor mental health. To assess intervention fidelity (Implementation), the research team will observe training sessions and complete a fidelity checklist to ensure all topics are covered and that the quality of the teaching is meeting expectations. The research team will observe all 14 instructors deliver the five training sessions (i.e., 1 x RBT, 2 x MHFA, 2 x Booster). The training program will also be monitored through regular weekly meetings between the research team, the instructors, and the training vendor.

### Instructors

The training program will be delivered by 14 instructors who are either accredited MHFA Master Instructors (conducted over 30 MHFA courses) or accredited MHFA Principal Master Instructors (Master Instructors must conduct over 10 MHFA courses in a 12-month period) in Australia and New Zealand. All instructors are accredited to deliver the Blended Online Financial Services Professionals MHFA course. Instructors will also undergo training to deliver the RBT.

### Data management and confidentiality

All participant data will be de-identified using a unique identifier to maintain anonymity. Results will be published in peer-reviewed journals and disseminated to the professional member bodies to communicate with their members. The Deakin University core research team (AN,GT,LS,SB,SHLT,CEV) will have access to the trial data set for the duration of the trial. All data will be kept electronically on a password protected server at Deakin University and securely stored for 5 years with AN and GT. Public access to the full protocol, participant level data-set and statistical code will be available upon request.

### Ethical principles

This study has been approved by Deakin University Human Research Ethics Committee (2020–399). It has been registered with ClinicalTrials.gov with the international standard randomised controlled trial number NCT04982094. Any amendments to the protocol will be approved by the Ethics Committee, will be communicated with ClinicalTrials.gov and any other relevant party (i.e., trainers, participants).

### Trial governance

Appropriate governance structures have been developed to ensure the research team is able to access the advice and guidance provided by each partner organisation that includes WorkSafe Victoria, Beyond Blue, MHFA Australia, The Australian Treasury, CAANZ, CPA, ICB and IPA. A steering committee will be formed consisting of representation from the research team and the eight partner organisations. In addition, the Council of Small Business Owners Australia (COSBOA) has also agreed to be represented on the steering committee. They will play a key role in ensuring this work is grounded in the realities of SME owners (including those who have [or have had] mental health conditions). A small business consultant with high level expertise in working with SME owners and their business advisors will also be employed on a fractional basis (0.1) to work with the steering committee to identify high-impact knowledge translation strategies that can address the needs of both SME owners and their intermediaries. The steering committee will meet on a quarterly basis to oversee trial conduct and monitor data collection. A collaborative decision-making process will used to ensure all members are actively involved in overseeing the project. Investigators will provide an annual report to the Ethics Committee and NHMRC, which will include interim data analysis, any unintended effects of the trial and raise any need to stop the trial.

### Incentives

Business advisors will be incentivised to take part in the training by obtaining continuing professional development (CPD) points that will count towards fulfilling their biennial professional membership requirements, certification as a mental health first aider, and a $30 gift voucher for completing surveys 2 and 3. SME owner participation will be incentivised with a $25 gift card for each survey they complete. One-hundred-dollar gift cards will also be provided to SME owners and business advisors who agree to be interviewed as part of the process evaluation. For SME owners and business advisors who are Australian residents and complete all 3 surveys, they will have a chance to win a $6000 AUD travel voucher via a prize-draw.

### Randomisation

Simple random allocation will be used to ensure the sample size is balanced across the two groups (1:1). Should differential attrition arise part-way through the project, i.e., due to a preference to partake in the intervention, the allocation ratio will be adjusted to compensate for this, i.e., a 1:2 ratio (MHFA+RBT: MHFA). The membership engagement officer at each business advisor’s member organisation (i.e., CAANZ, CPA, IPA, ICB) will conduct the randomisation process by providing eligible participants with a computer-generated unique numeric ID and allocating them to RBT + MHFA or MHFA alone. The participant’s names will be concealed throughout this process. Allocation concealment will be achieved because the member organisations will be unable to predict the unique ID allocated to each participant before they are sorted and randomised to a group. Participants will use their unique ID for completing the surveys, and the researchers will not have access to the business advisor’s contact details only unique ID, group allocation and survey results. Any contact will occur via member bodies or training vendor.

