### Inclusion criteria

The business advisor sample will be selected according to the following inclusion criteria: any qualified business advisor from Australia or New Zealand who provides business-related advice to a small-medium enterprise (SME) client. Business advice refers to the information, guidance and/or assistance provided by an external advisor that either directly or indirectly helps to prevent/reduce the financial pressures experienced by SME owner-clients. The SME owner client must be the owner-manager of the business (i.e., non-operational owners or ‘silent partners’ are not included) and the business needs to employ 1–199 employees. The business advisor must be in contact with their client at least three times a year. The exclusion criteria will be any business advisor who has completed Mental Health First Aid training within the last two years.

Because of our recruitment strategy, eligible participants will be randomised to one of two arms prior to receiving a generic invitation to join the study. They will be informed what study arm they are in, after they have agreed to participate. Thus, participants will only be blind to group allocation prior to providing consent to avoid self-selection bias. Participants must read a plain language statement and sign an online consent form hosted by Deakin University prior to starting (Supplementary file 2). Participants can withdraw at any time by contacting the research team at Deakin University.

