### Statistics

A report of the findings will follow CONSORT guidelines. The quantitative analysis will examine whether the magnitude of change in primary and secondary outcomes is different between the SME owners and their business advisors randomly allocated to the MFHA or RBT + MHFA arm (i.e., between-group differential change). Population average models, using a generalised estimated equation (GEE) approach accounting for within-individual repeated measures, will be used to assess for a treatment effect in the primary outcome. The analysis will employ an unstructured correlation structure for the GEE analysis and include a robust covariance matrix estimator, or Sandwich estimator, to provide a consistent estimate of the treatment effect. The GEE approach models the average response of the population rather than modelling the within-subject covariance structure, and unlike a basic regression model, it does not require distributional assumptions. It considers the correlation of within-subject data (longitudinal data) by using all available data for each subject, and it can be used on data with non-normal distributions. The GEE model will contain the fixed effect of intervention allocation and nominal time points as the main effects, and a two-way interaction between intervention allocation and time. The two-way interaction will estimate the effect of differential change from baseline measure in the intervention compared with control group at 2- and 6-months measurements. The GEE model will compare the between-group mean change for business advisors from baseline to 2-months (1-month post-training), baseline to 6-months (4 months post-training), 2-months to 6-months to test the hypothesis (i.e., the two-way interaction between intervention allocation and measurement at 2-months and it’s 95% confidence interval). For SME owners, the between-group differential change will be assessed from baseline to 6-months, baseline to 12-months, and 6-months to 12-months.

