In unblinded randomised control trials, participants allocated to the control group who are aware of a more desirable treatment group, may be envious of participants in the treatment group and be less willing to complete surveys [38, 39]. Because of the appeal the new RBT may offer to business advisors, we anticipate that participants in our MHFA alone group may be unmotivated to attend training sessions, complete surveys and ultimately dropout. If such a trend is observed in this study, we may take a pragmatic decision to change the random allocation ratio to allocate more participants to MHFA alone to have equal number of participants in both groups to enhance statistical power. If such a change in the allocation ratio is needed (e.g., from 1:1 to 1:2 to account for differential attrition), the participants will no longer have an equal chance of receiving each of the treatments. Bias could also arise if participants differ in important characteristics, hence the data from these two parts of the trial will be tested for homogeneity. If any significant differences are identified, the results will be analysed separately and then combined, as in a meta-analysis [40].

All analyses will be tested with a significance level of *p* < 0.05 by using the intention to treat principle. Participants classified as lost to follow-up will be compared with the study group for baseline demographic data using ordinary t test and χ2 test for homogeneity. A sensitivity analysis will be conducted to investigate the impact of dropouts on our primary hypothesis. Magnitude of change will be estimated through effect sizes using Cohen’s guidelines, whereby a value of 0.2 denotes a small, 0.5 a medium, and 0.8 a large effect size [41–43]. Data will be entered into Excel using Microsoft Office (version 16.0.1). Professional for Windows XP and StataSE (version 16) software for statistical analysis.

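### Simple allocation cannot ensure 1:1 balance (a wording fault), but a switch to 1:2 would tie enrolment period to arm, and the analysis separates the periods only if a homogeneity test is significant

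*Protocol article*

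**What the plan says.** **Method and its stated purpose (Protocol article, Randomisation).** "Simple random allocation will be used to ensure the sample size is balanced across the two groups (1:1"). No blocking or stratification is described.

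**Who allocates (Randomisation).** The membership engagement officer at each advisor's "member organisation (i.e., CAANZ, CPA, IPA, ICB) will conduct the randomisation process". There are four such bodies.

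**When (Inclusion criteria).** "eligible participants will be randomised to one of two arms prior to receiving a generic invitation to join the study".

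**Possible change of ratio (Randomisation, repeated in Statistics).** If attrition differs between arms part-way through, "the allocation ratio will be adjusted to compensate for this, i.e., a 1:2 ratio (MHFA+RBT: MHFA"). Neither section says whether the change would take effect in all four bodies on the same date.

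**Primary model (Statistics).** "The GEE model will contain the fixed effect of intervention allocation and nominal time points as the main effects, and a two-way interaction" of the two. Neither member body nor allocation period is listed.

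**Analysis after a ratio change (Statistics).** The two parts of the trial are tested for homogeneity. Only if significant differences appear, "the results will be analysed separately and then combined, as in a meta-analysis".

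**The concern.** Three matters of unequal weight meet here.

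1. The protocol credits simple randomisation with a property that belongs to restricted methods such as blocking.
2. Allocation is carried out body by body, yet the model carries no term for body. This invites the question whether accountants and bookkeepers could be unevenly spread over the arms without correction.
3. Once the ratio changes, an advisor's chance of entering each arm depends on when that advisor was allocated. Early and late entrants are then mixed differently in the two arms. Recruitment runs over 18 months (Recruitment section), and the Discussion relies on randomisation to minimise confounding by events such as lockdowns. With a changed ratio, that protection holds within each period but not across the pooled periods, unless the analysis takes account of period.

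The third matter is the only one that can bias the treatment contrast.

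**Working it through.** **Inputs.** From Sample size and power analysis: d = 0.20, mean difference 1.52, SD 7.60, two-sided α = 0.05, 80% power, 786 evaluable, 20% attrition, 984 recruited. From Randomisation: 1:1, possibly changed to 1:2 (combined arm to MHFA alone). The timing of a switch, the share of each body and any difference between periods are not given, so they are assumed below and labelled as such.

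**Step 1: the plan's own figure.** n per arm = 2(1.960 + 0.842)² / 0.20² = 392.4, rounded up to 393, so 786 in total. 393 / 0.8 = 491.25, rounded up to 492 per arm, so 984. Both figures reproduce.

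**Step 2: what simple allocation delivers.** Arm size follows Binomial(984, 0.5), if uptake after allocation is equal in both arms.
- SD = √984 / 2 = 15.7.
- 2.5% and 97.5% points: 461 and 523.
- Probability of exactly 492:492: 2.5%.
- Probability of a split worse than 55:45: 0.16%.

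Scaled to 786 evaluable, 461:523 becomes about 368:418. Noncentral t power is 79.96% at 393:393 and 79.80% at 368:418, a loss of about 0.2 points.

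**Step 3: member body under constant 1:1.** Every advisor has probability 0.5 whatever the body, so body and arm are independent by design. Chance imbalance has mean zero and is already part of the standard error. If one body held 10% to 50% of the sample and differed from the rest by 0.2 to 0.5 SD (assumed), the random error it adds has SD b√(4s(1−s)/786), with s the share and b the difference. This gives 0.004 to 0.018 SD, or 2% to 9% of d = 0.20. It costs precision and causes no bias.

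**Step 4: period after a switch to 1:2.** Assume the switch comes after half of all allocations.
- Combined arm: 0.5 × 1/2 + 0.5 × 1/3 = 0.4167 of all advisors. Later-period share = 0.1667 / 0.4167 = 40%.
- Control arm: 0.5 × 1/2 + 0.5 × 2/3 = 0.5833 of all advisors. Later-period share = 0.3333 / 0.5833 = 57%.
- Difference: 17.1 percentage points.

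Dropout that differs between arms leaves these shares unchanged, provided that each arm loses the same fraction in both periods.

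If change from baseline differs between periods by δ SD for reasons unrelated to arm, the pooled arm-by-time contrast shifts by 0.171δ:

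| δ (assumed) | Shift, SD | Share of d = 0.20 | Shift × 7.60, scale points |
|---|---|---|---|
| 0.2 | 0.034 | 17% | 0.26 |
| 0.5 | 0.086 | 43% | 0.65 |

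**Step 5: member body after a switch.**
- *One date for all bodies.* If a body's share of recruits rose from 10% before to 40% after (assumed), it would form 0.6 × 10% + 0.4 × 40% = 22.0% of the combined arm and 3/7 × 10% + 4/7 × 40% = 27.1% of the control arm, a gap of 5.1 points. Within each period body and arm remain independent, so adjusting for period removes this.
- *Different dates.* If one body with 25% of the sample were at 1:2 and the rest stayed at 1:1 (assumed), its share would be 18.2% of one arm and 30.8% of the other; with 50% of the sample, 40.0% and 57.1%. If bodies differ by 0.2 to 0.5 SD in change over time (assumed), the shift is 0.025 to 0.086 SD.

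**Step 6: does the homogeneity test protect?** The article does not say what is compared. If the test compares treatment effects between periods, it does not target δ at all, because a common difference between periods is not an interaction with arm. If it compares mean change between two halves of 393 with the design SD, its power at δ = 0.2 is the design power of 80%, because the arithmetic is that of Step 1. It would then miss such a difference one time in five.

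**The case against.** **What stands.** At this size simple randomisation is an accepted choice and its cost in power is negligible. Leaving member body out of the model is not an error under constant 1:1. Further covariates may properly be left to an analysis plan that is not shown. The ratio is changed to offset differential attrition, not chance imbalance, so blocking would not remove the reason for it. Because allocation precedes invitation and consent, blocked lists would not guarantee equal enrolled arms either. The planned contrast is a change from baseline, so stable differences between periods or bodies largely cancel and only differences in change matter. The Statistics section does anticipate a ratio change and offers a remedy. A large difference such as 0.5 SD would almost surely be found by a test that looked at change directly.

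**What does not dispose of the point.** The remedy is conditional. Arm and period are associated by construction once the ratio changes, so whether to stratify need not be learned from a significance test, and a non-significant result does not show that pooling is safe.

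**Stronger readings that the documents do not support.** A reader might infer that omitting member body invalidates the primary model, that the four bodies will switch at different times, or that the allocation scheme must be rebuilt. The first fails by Step 3. The second is not stated: the text speaks of one allocation ratio and of two parts of the trial, which suggests a single changeover. The third is out of proportion. The trial started in February 2021 with recruitment planned over 18 months, and the article appeared in June 2022, so a new scheme would come late for a gain of about 0.2 points of power.

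**Conclusion.** The point holds in limited form.

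- **Wording.** The claim that simple allocation secures balance is wrong. The consequence is negligible: 461 to 523 per arm, about 0.2 points of power.
- **Member body.** Under constant 1:1 the listed model is valid. Adding body would be an optional gain in precision, and nothing in the article allows its size to be estimated.
- **Ratio change.** This is the part with substance, and it is conditional. If the ratio moves to 1:2, allocation period becomes associated with arm (40% against 57% for a half-way switch). Member body does too if bodies recruit at different rates or switch at different times. The pooled analysis then has no unconditional correction.

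The illustrative bias of 17% to 43% of the design effect rests on an assumed half-way switch and an assumed difference between periods of 0.2 to 0.5 SD in change over time. If the ratio stays at 1:1, or change is the same in both periods, there is no bias. Severity is low, but the remedy is cheap.

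**What to change.** 1. In Randomisation, say that the arms are expected to be balanced.
2. State that any change of ratio takes effect in all four member bodies on one recorded date.
3. In Statistics, state that if the ratio changes, the primary model will always include allocation period (the ratio in force when the advisor was allocated) and member body, each with its interaction with time. An equivalent rule is always to estimate the effect within each period and combine the two. Neither should depend on the homogeneity test, which can stay as a descriptive check.
4. If the ratio never changes, member body and its interaction with time may be added for precision, provided that this is fixed before the data are analysed.

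**Cost.** A few extra parameters in a model with several hundred advisors, and a few sentences of text. Member body and allocation date should be recoverable from the bodies' allocation lists. The allocation scheme and the timing of randomisation stay as they are.

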### Recruitment

#### Business advisory professionals

The recruitment of business advisors into the online training program, Counting on U, will be conducted over 18 months via membership of their respective professional organisation (i.e., Chartered Accountants of Australia and New Zealand (CAANZ), Certified Practicing Accountants (CPA) Australia, Institute of Public Accountants (IPA), Institute of Certified Bookkeepers (ICB)). Representatives from each organisation will invite their members via email to participate in the training and research program. The project will also be advertised through Deakin University and professional organisations’ newsletters, websites, and social media pages.

Convenience sampling will be used, with all respondents who meet the inclusion criteria offered places in the training program until a total of 984 participants have been recruited. The research team will monitor the participants’ location in urban/regional/rural areas and state, and if a selection bias has occurred, advertising will be targeted to these underrepresented groups. All business advisors will be requested to complete a short online survey at three time-points: baseline, 2 months, and 6 months post-training (equivalent to 1- and 5-months follow-up post-training) (Figs. 1 and 2).

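### Unpredictable IDs do not establish allocation concealment when the member organisation allocates the arm before it sends the invitation

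*Protocol article*

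**What the plan says.** The protocol article describes the procedure in three places.

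- **Randomisation: who allocates.** The task belongs to a membership engagement officer at each professional body, who carries it out "by providing eligible participants with a computer-generated unique numeric ID and allocating them to RBT + MHFA or MHFA alone".
- **Randomisation: why this counts as concealed.** The reason given is "Allocation concealment will be achieved because the member organisations will be unable to predict the unique ID allocated to each participant", up to the point at which the IDs are sorted and randomised. The section also says that participants' "names will be concealed throughout this process".
- **Randomisation: contact.** Researchers see the ID, the group and the survey results but no contact details. "Any contact will occur via member bodies or training vendor".
- **Inclusion criteria: timing.** "eligible participants will be randomised to one of two arms prior to receiving a generic invitation to join the study". Advisors learn their arm once they have agreed to take part, and they consent on a form hosted by the university.
- **Recruitment, Business advisory professionals: who invites.** "Representatives from each organisation will invite their members via email to participate in the training and research program".

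The abstract says that recruitment was still under way at publication.

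**The concern.** Allocation concealment means that the people who bring participants into a trial cannot know or influence the arm until enrolment is complete. Being unable to foresee an ID before randomisation is enough only if enrolment is settled by then. In this trial advisors are randomised first and invited and consented afterwards, so the period that needs protection is the one after allocation. The stated reason does not speak to that period.

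Because randomisation precedes consent, the advisors who consent are a subset selected after randomisation. The two arms remain comparable only if invitation and any handling before consent are the same in both. If someone on the recruiting side could see the arm, that would rest on goodwill rather than on procedure. Comparing changes from baseline, as the Statistics section plans, removes a difference in starting level. It does not remove a difference in how much the consenting advisors were likely to change.

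The protocol also regards the two arms as unequally attractive: the Randomisation and Statistics sections both plan for a preference for the combined training. That passage is about participants and drop-out, not recruiters, but it shows that the arm is not a neutral label in this setting.

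**Working it through.** No arithmetic applies to the claim itself. The check is to put the steps in order and ask, at each one, who holds the arm.

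1. **Before randomisation.** IDs are computer-generated and the member organisation cannot foresee them. The concealment sentence covers this step, and it is adequate here.
2. **Randomisation.** An officer of the member organisation issues the ID and assigns the arm (Randomisation). From this moment the ID-to-arm list exists inside the member organisation. Names are hidden during this step.
3. **Invitation.** Representatives of the same organisation email their members (Recruitment). An email must go to an identifiable member, and participants use their ID for the surveys, so someone has to link ID to person. Researchers hold no contact details (Randomisation), so the link must lie with the member body or the training vendor. The article does not say which, nor whether that person can also see the arm.
4. **Contact before consent.** Any contact runs through member bodies or the training vendor (Randomisation). No access rule is stated for either.
5. **Agreement and consent.** The advisor agrees and signs online and is then told the arm (Inclusion criteria). The advisor is blind up to this point.

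The safeguards set against these steps:

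| Safeguard stated | Step covered | Who is kept from the arm |
|---|---|---|
| IDs cannot be predicted | 1 | Member organisation, before allocation only |
| Names hidden | 2 | Prevents the officer from matching a person to an arm while randomising |
| Generic invitation | 3 | The advisor |
| Arm disclosed after agreement | 5 | The advisor |

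No stated safeguard covers the recruiting side in steps 3 and 4. These are the steps between allocation and enrolment.

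For scale only, the trial is sized on a standardised difference of 0.20, which with the quoted SD gives 0.20 × 7.60 = 1.52 points (Sample size and power analysis). The target effect is small. The document contains nothing from which a selection effect could be estimated and compared with it. The planned 786 evaluable and 984 recruited advisors do not depend on this point.

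**The case against.** A reader might infer that the same body handles all contact and that the recruiters therefore know each advisor's arm. The document supports neither statement. Contact is through member bodies or the training vendor. The allocator is a membership engagement officer and the inviters are called representatives, and nothing says that they are the same people or that the inviters see the list. Names are said to be hidden during randomisation.

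The routes by which bias could enter are also thinner than in face-to-face enrolment. The invitation is uniform, advisors respond and consent online, and no reminders before consent are described. Targeted advertising is steered by location, with no link to arm. On eligibility the text points both ways: the Inclusion criteria speak of eligible people being randomised, which puts eligibility before allocation, while the Recruitment section offers places to respondents who meet the criteria, which suggests a check after the invitation. The point does not rest on that route.

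It can also be said that custody of the list is operational detail that an article leaves to the full protocol. That would be a good answer if the article had been silent. It instead claims concealment and gives a reason, and the reason does not reach the period that matters. This part of the concern stands.

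**Conclusion.** The concern holds in a limited form. The article claims allocation concealment on a ground that covers only the time before randomisation, while its own sequence places allocation, inside the inviting organisation, ahead of invitation and consent. The other measures reduce the risk and blind the advisor, but nothing stated shields the allocation from those who invite or handle contact before consent. Concealment up to enrolment is therefore asserted rather than secured.

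The document does not show that concealment was broken, and neither the direction nor the size of any bias can be derived from it. The conclusion rests on reading the three sections as one procedure, and on the assumption that no access restriction exists beyond those stated. If the full protocol keeps the list from inviters and from the vendor until consent, the remaining fault is only the wording of the concealment sentence.

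**What to change.** **For remaining recruitment**

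- The research team generates and holds the ID-to-arm list. It already has IDs and allocations without contact details, so no researcher blinding is lost.
- Member bodies attach IDs to members and send the generic invitation with no access to the list. The training vendor likewise has no access before consent.
- The arm is released by ID only after online consent, and preferably after the baseline survey.
- The concealment sentence is rewritten to say who generates and holds the list, who links IDs to names, and when the arm is released.

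**For advisors already invited**

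- State who held the list and whether those inviting or answering members could see the arm.
- Report numbers invited and consented by arm. A marked difference in consent proportion would be a warning sign. Similar proportions would be reassuring but would not prove that the consenting advisors are alike.

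**Cost.** The IDs and the university-hosted consent form already exist, and what changes is mainly who holds the list. A release step has to be added to the consent process, which the article does not describe at present. Arm-specific training sessions can be booked only after release. Sample size and the planned analysis are unchanged.
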